## Abstract

**Background:**

Photobiomodulation using low-level laser therapy (LLLT) has been tested as a new technique to optimize recovery of patients with traumatic brain injury (TBI). The aim of this study is to evaluate inhibitory attentional control after 18 sessions of active LLLT and compare with the placebo group (sham LLLT). Our exploratory analysis will evaluate the efficacy of the active LLLT on verbal and visuospatial episodic memory, executive functions (working memory, verbal and visuospatial fluency, attentional processes), and anxiety and depressive symptoms compared to the sham group.

**Methods/Design:**

A randomized double-blinded trial will be made in 36 patients with moderate and severe TBI. The active LLLT will use an optical device composed of LEDs emitting 632 nm of radiation at the site with full potency of 830 mW. The cranial region with an area of 400 cm^2^ will be irradiated for 30 min, giving a total dose per session of 3.74 J/cm^2^. The sham LLLT group contains only an LED device with power < 1 mW, only serving to simulate the irradiation. Each patient will be irradiated three times per week for six weeks, totaling 18 sessions. Neuropsychological assessments will be held one week before the beginning of the sessions, after one week, and three months after the end of LLLT sessions. Memory domain, attention, executive functioning, and visual construction will be evaluated, in addition to symptoms of depression, anxiety, and social demographics.

**Discussion:**

LLLT has been demonstrated as a safe and effective technique in significantly improving the memory, attention, and mood performance in healthy and neurologic patients. We expect that our trial can complement previous finds, as an effective low-cost therapy to improve cognitive sequel after TBI.

**Trial registration:**

ClinicalTrials.gov, NCT02393079. Registered on 20 February 2015.

## Background

### Epidemiology

Traumatic brain injury (TBI) is one of the main problems in the public health system due to its magnitude and clinical and social consequences [1]. It is the main cause of disability in young adults, with an estimated 2 million visits to emergency services in the United States in 2009 [2]. In low-income countries, the rate of TBI, especially due to motor vehicles, are > 80% of all cases, leading to higher costs and disabilities [3, 4]. In Brazil, the incidence of TBI is 65.6/100,000 inhabitants per year; however, this incidence appears to be underestimated due to the lack of methodology or inadequate documentation of medical records [5].

### Clinical and functional problems due to TBI

TBI is an alteration in brain function, or other evidence of brain pathology, caused by an external cause [6]. The trauma can result in long-lasting disability, even in people with mild TBI [7].

Long-term neurological and cognitive deficits are expected, including a variety of cognitive impairments, such as in learning, executive function including working memory [8, 9] and verbal fluency [10], reaction time, perceptual organization [11], attention, verbal and visual episodic memory [12, 13], depression, anxiety [8, 9, 14], fatigue, sleep disorders, and attention deficit [15]. Those symptoms are associated with loss of functionality,absence from work, and personal and social privations [16, 17].

### Rationale for the photobiomodulation using low-level laser therapy (LLLT) in patients with TBI

Considerable evidence has shown that the brain has an extensive ability of reorganization after damage [18]. Non-invasive brain stimulation (NIBS) can modulate brain plasticity after trauma through increasing synaptic strength, modulating neurotransmitters, and modifying neural networks [18–21]. LLLT is a technique of NIBS that the irradiation of specific infrared wavelengths is able to penetrate deeply into the brain [22]. These effects produce many biological responses, such as affecting the forming of adenosine triphosphate (ATP), increasing deoxyribonucleic acid (DNA) and ribonucleic acid (RNA), releasing nitric oxide (NO), cytochrome c oxidase (CCO), regulating reactive oxygen species (ROS), and modifying intracellular organelle membrane activity particularly in mitochondria, calcium flux, and stress proteins [23–25]. LLLT produces a shift toward higher oxidation in the overall cell redox potential [26] and briefly increases the level of ROS [27]. This change in the redox state of the mitochondria regulates several transcription factors [28]. These include redox factor-1 (Ref-1), cAMP response element (CREB), activator protein 1 (AP-1), p53, nuclear factor kappa B (NF-jB), hypoxia-inducible factor (HIF-1), and HIF-like factor [28]. The activation and regulation of redox-sensitive genes and transcription factors are thought to be caused by ROS induced from LLLT [27]. In turn, both ATP levels and blood flow increase, improving oxygenation found in damaged areas of the brain [28]. In animal models, LLLT has been investigated as an alternative treatment for brain injury, increasing neurogenesis after TBI [29] and showing a protective effect for stroke [30] and benefits for acute ischemic stroke, acute myocardial infarction, injured peripheral nerves, and spinal cord injury [31–33]. Previous studies showed the safety of photobiostimulation in humans [34], including promising interventions for acute stroke [34], TBI [17, 35–37], and dementia [38]. However, to date, just one open-label clinical trial studies the effect of LED therapy on improving cognitive function in patients with TBI [37]. Likewise, no randomized controlled trial studied the short-term and long-term effects of LLLT on the cognition of closed TBI patients.

### Objective

The aim of this study is to evaluate inhibitory attentional control after 18 sessions of active LLLT and compare with the placebo group (sham LLLT). Our exploratory analysis will evaluate verbal and visuospatial episodic memory, executive functions (working memory, verbal and visuospatial fluency, attentional processes), and anxiety and depressive symptoms.

## Methods

### Study design

This is a prospective, multicenter, randomized, parallel placebo-controlled trial that will be conducted at the Clinics Hospital, University of São Paulo (HC-FMUSP) and Salgado Institute, Londrina, Brazil. The protocol is registered on clinicaltrials.org (number NCT02393079). The trial will follow the CONSORT (Consolidated Standards of Reporting Trials) guidelines as well as SPIRIT (Standard Protocol Items: Recommendations for Interventional Trials) guidelines (Fig. 1). Figure 2 provides all information about patient enrollment, interventions, and follow-ups.

**Fig. 1 Fig1:**
[figure not shown]
Standard Protocol Items: Recommendations for Interventional Trials (SPIRIT): enrollment, assessment, interventions, and data collection. BDI-II: Beck Depression Inventory, 2^nd^ edition; BAI: Beck Anxiety Inventory; TMT A and B: Test Trail Making form A and B; COWAT: Controlled Oral Word Association Test; SNL: Sequence of Numbers and Letters; DSST: Digit Symbol Substitution Test; RAVLT: Rey Auditory Verbal Learning Test

**Fig. 2 Fig2:**
[figure not shown]
Flowchart of the LLLT study

### Eligible participants

#### Inclusion criteria

Patients of both genders;Age range 18–60 years;Glasgow Coma Scale (GCS) ≤ 12 at admission in the emergency room;Computer tomography (CT) or magnetic resonance imaging (MRI) consistent with closed TBI, including intracranial hematoma, subdural hematoma, epidural hematoma, diffuse axonal injury, hemorrhagic contusion, and subarachnoid hemorrhage;Loss of consciousness ≥ 30 min;Post-traumatic amnesia of ≥ 24 h;Outpatients with > 6 months TBI;Signed informed consent.

#### Exclusion criteria

Metal implant or device in the brain or scalp;Uncontrolled epilepsy;Non-consent sign;Portuguese not their first language;Non-comprehension and/or not able to follow instructions.

#### Recruitment

The patients will be contacted and invited to participate before or after their regular appointment at the Neurotrauma Outpatient Clinics at the HC-FMUSP or by a contact list of provided by the acute Neurotrauma Inpatient Section at the HC-FMUSP. The patients will give verbal consent before attending their first consent visit.

### Study intervention

#### Standard care

All patients will keep their clinical follow-up at the Neurotrauma Outpatient Clinics at HC-FMUSP or at Salgado Institute, Brazil, independently of the study group assignment or decision of dropping out. A trained research nurse and a psychologist introduced the trial to patients informing them of the principles, objectives, and safety/harm. A trained physical therapist will also conduct and follow the patients along the trial.

All information related to patients (i.e. data analysis, anthropometrical measures, reports, and other relevant information) will be stored in locked file cabinets in areas with limited access. These files will be identified with a code ID and only researchers of this study will have access to this information.

#### LLLT intervention

Two optical and identical devices (helmets) will be used for the intervention (Fig. 3). For the active optical device, a helmet configured with 13 sets of LEDs at a 632-nm wavelength will distribute a total optical radiation of 830 mW over the skull surface. The skull area receiving irradiation is approximately 400 cm^2^ during 30 min, in which the total expected dose per session is 3.74 J/cm^2^. However, only 3.1% of this energy reaches the gray matter [39].

**Fig. 3 Fig3:**
[figure not shown]
**a** Two identical helmets, active and sham stimulation. **b** The inside view of the active LLLT helmet

The rationale follows: optimal wavelength penetration within biological tissues, occurs with a wavelength range of 600–1000 nm [40]. The inactive helmet (sham) contains only LEDs with power < 1 mW, only serving to simulate the irradiation of the patient. All the patients will be submitted to 18 30-min LLLT sessions (active or sham condition), three times per week over six weeks. For safety, after the LLLT intervention, the patient will be asked about side effects between sessions.

#### Neuropsychological assessment

Patients will be assessed at baseline, one week after the end of the LLLT, and three months after the LLLT sessions. Each patient will follow the participation period as shown in Fig. 1.

Instruments:Beck Depression Inventory (BDI-II), used to assess depressive symptoms, classified as minimal (0–11 scores), mild (12–19), moderate (20–35), and severe (36–63) [41, 42];Beck Anxiety Inventory (BAI), used to assess anxiety symptoms, classified as minimal (0–7 scores), mild (8–15), moderate (16–25), and severe (26–63) [42];Trail Making Test A and B (TMT A and TMT B), used to measure attention, speed, and mental flexibility. In TMT A, the patient is instructed to draw a line from 1 to 2, 2 to 3, and so on. In TMT B, the patient switches between numbers and letters, drawing a line from 1 to A, A to 2, 2 to B, and so on. On both forms A and B, the patients perform a sample before the real test. The patient is instructed to perform as fast as he/she can [43];Stroop Test - Version Victoria, measuring cognitive control with each person can maintain a goal in mind and suppress a habitual response in favor of a less familiar one. The interference effect is determining by calculating the extra time required to name colors (Card 3) in comparison to the time required to name colors in the control task (Card 1) [43, 44];Controlled Oral Word Association Test (COWAT), used to evaluate the spontaneous production of words under restricted search conditions (verbal association fluency). For the phonemic fluency task, the patient must provide orally as many words as possible beginning with the letters F, A, and S for 1 min for each letter. For the semantic fluency task, the patient is asked to produce as many animals’ names as possible within 1 min. The total correct is the sum of all admissible words for the semantic category [43];Five-point test, this test requires preproduction of novel designs under time constraints (3 min). The score is calculated including the total number of unique designs and the number of repeated designs (perseverations) [45];Symbol Digit Modalities Test (SDMT) oral version, the test is used to assess divided attention, visual scanning, tracking, and speed. The examiner records the numbers that correspond with symbols. The number of correct substitutions within the 90-s interval is the score of the task [46, 47];Rey Auditory Verbal Learning Test (RAVLT), measures immediate episodic memory, learning, susceptibility to interference, and recognition memory. A list of 15 nouns (list A) is read aloud to the patient, for five consecutive trials, each followed by a free-recall test. An interference list of 15 words (list B) is presented, followed by a free-recall test of that list. Immediately after this, delayed recall of list A is tested (Trial 6), and after 20 min (Trial 7), without further presentation of those words. The recognition is performed by presenting 50 words containing words from lists A, B, and new words, and the patient needs to identity the words from list A [43, 48];Sequence Numbers and Letters (Wechsler subscale - WAIS-III), used to evaluate working memory, random numbers, and letters is presented orally to the patient and must be mentally organized and immediately reported to the examiner with the following rule: first the crescent numbers then the letters (in alphabetical order). In test difficulty increases the patients correctly perform the task [49];Digit Span (DS) Forward and Backwards (WAIS-III), the DS assesses working memory. For the DS forward, the patient hears carefully a sequence of numbers and must repeat it immediately in the same sequence as previously presented. For the DS backwards, the patient must repeat the sequence inversely. In both conditions the number of numbers presented increases as the patient hits two corrects scores from the same span [49];Rey-Osterrieth Complex Figure Test (ROCF), the purpose is to assess visual–spatial constructional ability and visual memory. The patient is required to copy the ROCF, and after 3 and 30 min, a white sheet is given to the patient, and asked to draw the amount of information retained over time [50, 51].

### Primary outcome

Inhibitory attentional control (time score) measured by Stroop test. The Stroop test is known to be an accurate assessment of executive function in mild to moderate TBI [52].

### Secondary outcomes

Verbal and visuospatial episodic memory;Executive functions (working memory, verbal and visuospatial fluency, attentional processes);Anxiety and depressive symptoms.

### Sample size

Based on the previous pilot study [37] that analyzed the cognitive function of patients with TBI after repetitive sessions of RED/Near-infrared LED treatment. Considering the improvement on Stroop test of 1 standard deviation (SD) related to the baseline, the level of significance of 0.05 and the power of 80%, 16 patients per group was estimated. Considering the rate of 15% of drop-outs, we added two participants per group, ending with a total sample of 36.

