### Randomization

All eligible recruited patients will be randomly divided into two groups with a 1:1 ratio and blocks of four and six performed by the co-investigator through the randomization list (randomization.com). The randomization list will be kept in safe storage with the co-investigator responsible for the stimulation sessions. She will provide the allocation concealment assignment for the patients. No information about the assigned group will be given for the patient or to the research assessor.

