## Discussion

The present study is designed to evaluate the effects of 18 sessions of LLLT over cognition, in patients with chronic moderate and severe TBI. Our primary hypothesis is that the sessions of active LLLT will improve attention (at least 1 SD) measured by Stroop test compared to the placebo group (sham LLLT). Our secondary hypothesis is that the active group will improve in all domains assessed by the neuropsychological battery, including cognition and mood, compared to placebo group.

LLLT can modulate many biological effects penetrating the scalp into the brain [25], playing a role improving the outcome of the patients in two different ways, depending on the stage of the trauma. In the acute phase after TBI, the initial neuronal injury occurs instantly and oftentimes causes irreversible damage to the central nervous system, due to impairment of neuronal cell functions, including mitochondria, and glia cells [18, 58]. The disruption of neuronal circuitry causes loss of connectivity between different areas of the brain and can negatively impact neural regeneration, leading to dysfunctional interactions. In the secondary stage after the trauma, other changes may occur, including release of neurotransmitters, decreased glucose utilization, lactic acid accumulation, reduced activity of ATP-reliant ion pumps, increased release of glutamate, Ca2 + −induced depolarization, and excitotoxicity [21, 58].

Previous studies showed improvement on cognition including attentional process and episodic memory after repetitive sessions of LLLT in patients with TBI [17, 37]. It seems that the LLLT decreases the inflammatory response, helping the neuroprotection after TBI. This process leads to increases on the ATP, cellular energy, and blood flow, decreasing the metabolic process. In summary, the LLLT seems to increase the intercellular synapses, acting as a possible treatment after acute and chronic TBI [37, 59–61].

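### Two extra patients per group cover about 11% drop-out, not the stated 15%: keeping 16 evaluable per group needs 19 (38 in total), so power at 15% loss is a little under the stated 80%

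*Protocol article*

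**What the plan says.** The Sample size section of the protocol article builds its figure in two steps. The first sets the effect and the error rates: "Considering the improvement on Stroop test of 1 standard deviation (SD) related to the baseline", with "the level of significance of 0.05 and the power of 80%, 16 patients per group was estimated". The second allows for attrition: "Considering the rate of 15% of drop-outs, we added two participants per group, ending with a total sample of 36". That makes 18 per group, and the Randomization section confirms equal allocation ("randomly divided into two groups with a 1:1 ratio").

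The section gives no formula, no test, no sidedness and no correlation between baseline and follow-up. It ties the 1 SD to baseline, but the Discussion states the primary hypothesis as a contrast between arms: "the sessions of active LLLT will improve attention (at least 1 SD) measured by Stroop test compared to the placebo group (sham LLLT". The Statistical analysis section plans a two-group by three-time repeated-measures ANOVA and regression imputation for missing data.

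**The concern.** The attrition rate and the allowance stand in the same sentence and do not agree. If 16 evaluable patients per group are needed and 15% are expected to be lost, 18 per group is one short. No later analysis plan can reconcile the two, because the text fixes both.

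The stake is how the result is read. The trial is small, and a null finding would be judged against a claim of 80% power. If attrition runs as the protocol expects, the number evaluable falls below the protocol's own requirement, and the power stated is not the power that the stated inputs give.

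**Working it through.** **Inputs.** From Sample size: effect 1 SD, significance level 0.05, power 80%, 16 per group, drop-out 15%, two added per group, total 36. From Randomization: 1:1 allocation. Two assumptions are needed. The 1 SD is a difference between arms, as in the Discussion, so d = 1. The test is two-sided.

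**Step 1: reproduce the 16.** Normal approximation for two means:

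n = 2 × (1.960 + 0.842)² / 1² = 15.70, rounded up to 16 per group.

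This matches the protocol. The alternatives do not: a one-sided test gives 13, and a paired test within one group gives 10. So the two-sided comparison between arms is the reading that fits the stated figure.

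**Step 2: the drop-out allowance.**

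- Dividing by the retained fraction: 16/0.85 = 18.8, so 19 per group, 38 in total.
- The simpler add-on: 16 × 1.15 = 18.4, again 19 per group.
- Loss that 18 per group can absorb: 2/18 = 11.1% (as an add-on to 16, 2/16 = 12.5%).
- Evaluable at the stated loss: 18 × 0.85 = 15.3 per group; 36 × 0.85 = 30.6 in total, against 32 required.

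Neither convention gives 18. A possible origin is 15% of 16 = 2.4, rounded down to 2; the document does not say.

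**Step 3: the effect on power.** The normal approximation is Φ(d√(n/2) − 1.960). The t-test figure comes from the noncentral t distribution with 2n − 2 degrees of freedom and noncentrality d√(n/2).

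| Evaluable per group | d√(n/2) | Power, normal | Power, t-test |
|---|---|---|---|
| 16 | 2.828 | 80.7% | 78.1% |
| 15.3 | 2.766 | 79.0% | 76.2% |
| 15 | 2.739 | 78.2% | 75.3% |

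Averaging over random, independent 15% drop-out from 18 + 18 gives 78.6% (normal) and 75.8% (t-test), in line with the table.

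**Step 4: sensitivity to the formula.** By the t-test, 17 per group gives 80.7% power, and 17/0.85 = 20 per group (40 in total). This changes the formula as well as the drop-out step, so it does not measure the drop-out slip alone.

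**The case against.** The strongest reply is that the slip is one patient per group and hardly matters. On the formula that reproduces the protocol's own 16, power at 15.3 per group is 79.0% against a stated 80%. No conclusion of the trial turns on that point. This stands, and it limits the weight of the finding.

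A second reply is that imputation keeps everyone in the analysis. It keeps the rows, but regression imputation does not restore the information lost with the missing outcomes.

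A third is that a repeated-measures analysis may have more power than a comparison at one time point. That is possible, but it depends on a baseline to follow-up correlation that the document does not give and that its 16 does not use. It cannot justify the stated allowance. For the same reason, one cannot say outright that the design lacks 80% power under every analysis; the supportable statement is that the stated inputs do not give the stated allowance.

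Two stronger readings should be resisted:

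- A reader might infer that the 16 is a second error because a t-test needs 17. The section names no test, and 16 is the correct normal-approximation answer. The t-test figures are a refinement.
- A reader might infer much lower power from the Bonferroni correction in Statistical analysis. That section names Bonferroni only as a post-hoc procedure, does not define the family of comparisons, and sets 0.05 as the threshold for all effects. One of the three time points is baseline, where no treatment effect can exist. No power figure at a divided significance level can be drawn from this text.

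**Conclusion.** The drop-out step is wrong as written. At 15% drop-out, 16 evaluable per group needs 19 randomised per group; the planned 18 allows for 11% and leaves about 15.3. This part is plain arithmetic on the stated figures and needs no assumption.

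The cost in power is modest. Compared with 16 evaluable, 15.3 per group loses 1.7 points by the normal approximation (80.7% to 79.0%) and 1.9 points by the t-test (78.1% to 76.2%). The wider gap, from the stated 80% to 75–76%, arises only when the drop-out slip and the change to a t-test are combined. All the power figures rest on the two assumptions listed with the inputs: a 1 SD difference between arms and a two-sided 5% test. They use no gain from repeated measures.

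This is a minor to moderate correction of a stated figure. It does not show that the trial is unsound or that more patients must be recruited.

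**What to change.** Keep 36 patients and restate the Sample size paragraph in one of two ways:

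- *With 36 randomised and 15% drop-out (about 15 per group evaluable), power is about 75–76% for a 1 SD difference between arms (two-sided 5% t-test; about 78–79% by normal approximation).*
- *The sample of 36 allows for 11% drop-out; with 16 evaluable per group, power is 78% for a 1 SD difference between arms (two-sided 5% t-test).*

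Either wording also settles what is now left open: that the 1 SD is a contrast between arms, that the test is two-sided, and which formula the power refers to. The cost is a rewritten paragraph and a slightly less favourable power figure. No patients are added, and nothing in the conduct of the trial changes.
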